### Sample size calculation

The PORSCH trial is a superiority trial. The effect of the intervention will be measured using the incidence of the primary endpoint (i.e. post-pancreatectomy bleeding, new-onset organ failure or death), which is expected to become lower after implementation of the algorithm. In this study, we aim to improve the outcomes of all patients undergoing pancreatectomy. However, to determine the superiority of the algorithm in a homogenous sample of patients, the sample size calculation was based on the cohort of patients undergoing pancreatoduodenectomy.

For sample size calculation we evaluated three Dutch datasets: the mandatory Dutch Pancreatic Cancer Audit (*n* = 1686), data from the study on management of pancreatic fistula (*n* = 309 patients [9]) and the validation study performed in preparation for this trial (*n* = 174). All outcome data used for sample size calculation are presented in Table 2. The composite primary endpoint occurred in 13.8% of patients in the Dutch cancer audit (2014–2015), in 44% of patients with severe pancreatic fistula after pancreatoduodenectomy [9] and in 17% in our own validation database (2016). For sample size calculation we used the lowest incidence that we identified in these three datasets (i.e. 13.8% from the audit data).

**Table 2 Tab2:** Composite primary endpoint

	DPCA	Management of pancreatic fistula	Validation database
Year(s)	2014–2015	2005–2013	2016
Patients	1686	309	174
Composite primary endpoint	12%	44%	15%
In patients undergoing pancreatoduodenectomy	14%	44%	17%
In patients undergoing distal pancreatectomy	7%	–	7%
Relative reduction between study groups	–	53%	–
Relative reduction between quartiles	62%	–	–

Incidence of the primary composite endpoint in three databases; “years” represents the time pancreatic resections were performed; “patients” represents the number of patients included in the analysis. “Management of pancreatic fistula” refers to Smits et al. JAMA Surg [9]. and includes only patients with severe pancreatic fistula; “validation study” refers to data used to validate the proposed algorithm

*DPCA* Dutch Pancreatic Cancer Audit

The expected reduction in the composite primary endpoint was evaluated in two datasets. A relative reduction of 53% was observed in the study on management of pancreatic fistula (i.e. 34% after primary catheter drainage versus 73% after primary relaparotomy). Using the Dutch Pancreatic Cancer Audit data, centers were divided into four quartiles based on the incidence of the primary endpoint after pancreatoduodenectomy. The incidence was 21% in the worst-scoring quartile containing 292 patients from four centers. The incidence of the composite primary endpoint was 8% (i.e. relative reduction 62%) in the best-scoring quartile containing 331 patients who underwent pancreatoduodenectomy in five centers. Based on these outcomes, a relative reduction of 50% in the primary endpoint was used for the sample size in the PORSCH trial. This was the minimal reduction deemed clinically relevant by the members of the trial steering committee and stakeholders from the Dutch Pancreatic Cancer Group.

The required sample size was calculated using the formula for stepped-wedge designs using an expected incidence of 13.8%, a relative reduction of 50%, two-sided alpha of 0.05 and power of 0.80 [30]. The intra-cluster correlation (ICC) estimated from the Dutch Pancreatic Cancer Audit was 0.009 (95% CI 0.006–0.049). As the within-period and between-period ICC were the same, the cluster autocorrelation was set at 1 [31]. Table 3 provides the required sample size for different numbers of participating sites (i.e. clusters). This number dictates the inclusion time in this study design, which was based on the total number of pancreatoduodenectomies performed in the last 2 years according to the Dutch Pancreatic Cancer Audit. As each cluster will contain one of the 17 participating centers, the number of sequences is equal to the number of clusters. Based on the annual number of pancreatoduodenectomies performed in The Netherlands in 2014 and 2015, the planned study duration is 92 weeks to include the required sample size of 1186 pancreatoduodenectomies with complete enumeration (i.e. 5.1 weeks per step for 18 time periods). The total duration of the trial will be 96 weeks, including a 4-week wash-in period.

**Table 3 Tab3:** Required sample size for different numbers of participating centers

Number of centers	Cluster size^**a**^	Required sample size	Expected inclusions	Inclusion time^**b**^
14	5.9	1239	1239	28
15	5.1	1220	1224	25
16	4.5	1204	1224	24
17	3.9	1186	1193	22

^a^ Average number of patients per center for every step in the stepped-wedge design

^b^ Inclusion time in months including 4 weeks wash-in phase

As we include patients undergoing all types of pancreatic resection in this trial, the total number of patients registered in this trial is expected to be 25% more than the required sample size. We will perform the primary analyses in patients undergoing pancreatoduodenectomy and subsequently in all patients undergoing any type of pancreatic resection.

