### Interim analysis

An interim analysis will be performed to evaluate the inclusion rate. At 50% of the planned time for inclusion, the total number of inclusions will be evaluated. If the sample size is less than 47.5% of the target at that time, the duration of steps in the design for the remaining part of the study will be prolonged such that power of 80% is maintained. If the sample size is adjusted at interim analysis, the adjusted dates for cross-over will dictate the allocation of patients to routine practice or best practice for the analysis.

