### Statistical analysis

For statistical analysis, outcomes of all patients undergoing pancreatic resection before implementation of the algorithm (i.e. current practice) will be compared to outcomes of all patients undergoing pancreatic resection after implementation of the algorithm (i.e. best practice). The date of pancreatic resection will determine the study phase in which a patient will be analyzed. The primary analysis will be on an intention-to-treat basis according to the planned date of cross-over to care according to the algorithm. Data from patients in the wash-in period will be excluded from the primary analysis. Secondary analyses include a per-protocol analysis in which we will compare patients who receive care according to the algorithm (i.e. all resections after first implementation presentation at a center, including patients undergoing pancreatic resection in the wash-in period) to patients undergoing pancreatic resection before cross-over. When appropriate, 95% confidence intervals will be calculated. In all analyses a two-sided value of alpha of 0.05 will be used to denote statistical significance.

Missing baseline data will be imputed using multiple imputation techniques. The primary analysis will be performed using the multiple imputed data. A complete case analysis will be performed to check for inconsistencies. Baseline data will be analyzed and reported using standard descriptive statistics. The chi-square or Fisher’s exact test is used to compare categorical variables as appropriate. Parametric continuous variables are presented as mean with standard deviation (SD) and are compared using Student’s *t* test. Non-parametric continuous variables are presented as median with interquartile range (IQR) and are compared using the Mann-Whitney *U* test.

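### The 80% power in the sample size section is for a design without the excluded wash-in; with the 4-week gap at each center, the same inputs give about 77%

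*Protocol article*

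**What the plan says.** All references are to the protocol article.

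- **Sample size calculation, method and inputs.** "The required sample size was calculated using the formula for stepped-wedge designs", with "expected incidence of 13.8%, a relative reduction of 50%, two-sided alpha of 0.05 and power of 0.80". The ICC is 0.009, with a 95% interval of 0.006 to 0.049, and "the cluster autocorrelation was set at 1". There are 17 centers, 17 sequences and 18 periods of 5.1 weeks, which gives 1186 pancreatoduodenectomies in 92 weeks.
- **Sample size calculation, wash-in.** "The total duration of the trial will be 96 weeks, including a 4-week wash-in period". The footnote to the inclusion time in Table 3 reads "Inclusion time in months including 4 weeks wash-in phase".
- **Statistical analysis.** "Data from patients in the wash-in period will be excluded from the primary analysis".
- **Whose wash-in it is.** Trial design describes it as training of the clinicians in the center that is crossing over. The per-protocol definition under Statistical analysis counts it from the first presentation at a center. The Discussion says that the algorithm was not circulated within centers before it. It is therefore a gap at each center's own switch, not one national pause.
- **Interim analysis.** If inclusions fall below 47.5% of the target at half time, the remaining steps "will be prolonged such that power of 80% is maintained".

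**The concern.** In a stepped-wedge trial with period effects, much of the information on the intervention comes from periods in which some centers have switched and others have not, and especially from the data around each center's switch. A 4-week exclusion takes 4/5.1 = 78% of one center-period from every center at that point. The plan compensates in calendar time. That restores the number of patients, but weeks in which every center is in the same phase say almost nothing about the effect.

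The 80% figure is stated for a 50% reduction, which the steering committee called the minimal relevant effect, so a shortfall applies to the very effect the trial is meant to detect. The interim wording also treats the patient count as if it carried the 80% with it.

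**Working it through.** **Inputs (Sample size calculation).** Incidences 0.138 and 0.069, difference 0.069; ICC ρ = 0.009; autocorrelation 1; K = 17 centers; T = 18 periods; N = 1186, so m = 1186/(17 × 18) = 3.876 per center-period. The total variance σ² is either pooled, 0.1035 × 0.8965 = 0.09279, or the average of the two arm variances, (0.138 × 0.862 + 0.069 × 0.931)/2 = 0.09160. Then τ² = ρσ² and σc² = (1 − ρ)σ²/m.

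**Step 1: reproduce the plan's figure, with no gap.** For a complete design with period effects and a random center intercept,

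Var = Kσc²(σc² + Tτ²) / [(KU − W)σc² + (U² + KTU − TW − KV)τ²],

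where U = 1 + … + 17 = 153 and W = V = 1² + … + 17² = 1785. So KU − W = 816, and U² + KTU − TW − KV = 23409 + 46818 − 32130 − 30345 = 7752.

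With the pooled variance, τ² = 0.000835 and σc² = 0.02373. The numerator is 17 × 0.02373 × 0.03876 = 0.01563 and the denominator is 19.36 + 6.47 = 25.83. Var = 0.000605, SE = 0.02460, and power = Φ(0.069/0.02460 − 1.96) = Φ(0.845) = 80.1%. The averaged variance gives 80.6%.

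The other Table 3 rows (14 centers/1239, 15/1220, 16/1204) also give 80.1–80.2% with the pooled variance. The expected-inclusions column is simply centers × periods × cluster size, for example 17 × 18 × 3.9 = 1193. Every center-period is counted in full.

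**Step 2: add the gap.** The model and accrual are unchanged: 1186/92 = 12.9 patients a week nationally, and one switch every 92/18 = 5.11 weeks. Four weeks are removed at each center's switch and the trial runs to 96 weeks. The variance is now the treatment element of (Σ Xₖ′Vₖ⁻¹Xₖ)⁻¹ over centers, where Vₖ has τ² everywhere plus (1 − ρ)σ²/n on the diagonal for each retained cell.

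| Design | Analysed N | SE (pooled / averaged) | Power |
|---|---|---|---|
| No gap, 92 weeks | 1186 | 0.02460 / 0.02444 | 80.1–80.6% |
| Gap, 92 weeks | 1134 | 0.02580 / 0.02563 | 76.3–76.8% |
| Gap, 96 weeks, 5.11-week steps | 1186 | 0.02575 / 0.02558 | 76.4–77.0% |
| Gap, 96 weeks, 18 steps of 5.33 weeks | 1186 | 0.02528 / 0.02511 | 77.9–78.5% |

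For the third row, Φ(0.069/0.02575 − 1.96) = Φ(0.720) = 76.4%. At 1193 patients it is 76.6–77.2%. The gap costs 4 × 12.9 = 52 patients; the added weeks return them, but power rises by only about 0.2 points.

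**Step 3: sensitivity, gap and 5.11-week steps.**
- ICC 0.006: 78.4–78.9%, against 82.0–82.5% without the gap.
- ICC 0.049: 67.2–67.8%, against 71.1–71.6% without the gap.
- Weekly time effects: 76.4–76.9%. Linear time: 76.5–77.0%.
- Gap before the switch, with the extra weeks at the start: 76.4–77.0%.

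**Step 4: scale of the shortfall.** Under this model, 80% with the gap would need steps of about 5.5–5.6 weeks, or about 1285–1300 analysed pancreatoduodenectomies.

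**The case against.** **Placement of the extra weeks.** The article does not say where they fall, and the design schematic is not reproduced in the text available. The stated 5.1-week step with 4 weeks added separately favors the 77% reading, but equal steps of 5.33 weeks would give about 78%. This stands, and it is why a range is given.

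**The model.** A reader might infer that the primary analysis as written has 77% power. The documents do not support that. Statistical analysis describes mixed-effects logistic regression with a random intercept and a random slope. The crude version has no time term; the adjusted version has continuous calendar time, time since cross-over and prognostic covariates. Without any time term the exclusion costs nothing (about 96% power either way in the linear calculation), though such a model is open to confounding by calendar time. A logistic mixed-model simulation with a hospital random intercept fell from 82.9% to 78.6% over about 600 runs each. That is the same direction and size, but with a Monte Carlo error of about 1.6 points per figure it cannot establish the loss alone. The 77% therefore corrects the stated 80% on its own terms; it does not forecast the power of the final model.

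**Margin elsewhere.** The plan used the lowest of three incidences. With the gap, a control rate of 17% (the validation cohort) gives 85–86%, and a 53% reduction gives 82%. The ICC interval alone moves power by about 11 points. All true, but the 80% is stated for 13.8%, a 50% reduction and ICC 0.009, so favorable values of other inputs do not make that figure correct.

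**The interim.** Trial status reports that it was held on 8 November 2018 and led to no adaptation. Nothing here shows that decision to be wrong, and changing the rule now would serve no purpose.

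**Conclusion.** The concern holds in limited form. The 1186 patients and 80% power belong to a complete stepped-wedge design, while the analysis section removes 4 weeks at each center's switch. On the plan's own inputs and the period-adjusted random-intercept model behind its formula, power at 1186 to 1193 analysed patients is about 77% with 5.1-week steps and about 78% with 18 equal steps: a loss of roughly 2 to 4 points. The added 4 weeks repair the count, not the power.

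This rests on a wash-in of 4 weeks at every center, constant accrual, equal center sizes and a normal approximation. A reader might conclude that the trial is seriously underpowered or must recruit more. The documents do not support that: the shortfall is modest and smaller than the uncertainty from the ICC, and it changes neither the analysis nor the treatment comparison. It is a figure to correct.

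**What to change.** 1. In Sample size calculation, state that 80% refers to the design before the wash-in is excluded. Give the power at the planned number of patients as about 77% (77–78.5% depending on where the extra weeks fall), computed with an incomplete stepped-wedge variance that has a 4-week gap per center. Say where the 4 weeks fall.
2. Give the range over the ICC interval: with 5.1-week steps, 78–79% at 0.006 and 67–68% at 0.049.
3. Keep the patient numbers in Table 3 and add the power with the gap for each row, with a footnote that the required sizes assume no excluded data.
4. In Interim analysis, note that reaching the full patient count does not by itself maintain 80% power. The interim need not be redone.

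The cost is a change of text and table and a slightly less favorable stated power. No extra patients, longer recruitment or change to the analysis is requested.

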**Methods:**

This is a nationwide stepped-wedge, cluster-randomized, superiority trial, designed in adherence to the Consolidated Standards of Reporting Trials (CONSORT) guidelines. During a period of 22 months, all Dutch centers performing pancreatic surgery will cross over in a randomized order from current practice to best practice according to the algorithm. This evidence-based and consensus-based algorithm will provide daily multilevel advice on the management of patients after pancreatic resection (i.e. indication for abdominal imaging, antibiotic treatment, percutaneous drainage and removal of abdominal drains). The algorithm is designed to aid early detection and minimally invasive step-up management of postoperative pancreatic fistula. Outcomes of current practice will be compared with outcomes after implementation of the algorithm. The primary outcome is a composite of major complications (i.e. post-pancreatectomy bleeding, new-onset organ failure and death) and will be measured in a sample size of at least 1600 patients undergoing pancreatic resection. Secondary endpoints include the individual components of the primary endpoint and other clinical outcomes, healthcare resource utilization and costs analysis. Follow up will be up to 90 days after pancreatic resection.

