### Subgroup and sensitivity analyses

Analyses will be performed both on the group of patients undergoing pancreatoduodenectomy and on the entire group of all patients undergoing pancreatic resection. Additional subgroup analyses will be performed based on adherence to the study protocol (i.e. proportion of patients’ days in which the algorithm is followed), hospital volume (> 45 vs. ≤ 45 pancreatic resections a year), pathologic nature of disease (malignant disease), in patients with postoperative pancreatic fistula and in patients with a high risk of pancreatic fistula [34].

A sensitivity analysis will be performed to evaluate the impact on outcomes related to postoperative pancreatic fistula. To this aim, the adjudication will be asked if an outcome was related to postoperative pancreatic fistula and if this outcome could have been prevented by adherence to the algorithm. Two separate analyses will be performed on the Comprehensive Complication Index: one analysis including all complications and one adjusted analysis, in which interventions imposed by the algorithm (e.g. minimal invasive catheter drainage and use of antibiotic management for abdominal sepsis) will not be included in the calculation. A sensitivity analysis will be performed to evaluate the success of implementation. Centers will be divided into equally sized clusters based on the percentage of additional abdominal CT scans per patient after implementation, as compared with before implementation. Separate analysis will be performed for each group.

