## Trial status

This manuscript is based on the PORSCH study protocol version 7, December 2017. The Medical Ethical Committees United (MEC-U) approved the study and waived the need for informed consent (reference number W17.057). Local approval for the study is obtained in all participating centers before recruitment starts.

First inclusion: 8 January 2018.

Interim analysis: 8 November 2018, 569 patients included. Conclusion: enrollment as planned, trial continues without adaptation.

Planned last inclusion: 9 November 2019.

Trial status at time of submission: recruiting.

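### The sample size section makes pancreatoduodenectomy the primary population, but the abstract and statistical analysis section describe all resections, with a total that does not reconcile and no rule linking the two tests

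*Protocol article*

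**What the plan says.** All places are in the protocol article.

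- **Sample size calculation.** The calculation rests on the pancreatoduodenectomy cohort, chosen for homogeneity, "using an expected incidence of 13.8%, a relative reduction of 50%, two-sided alpha of 0.05 and power of 0.80". For 17 centers this gives 1186 pancreatoduodenectomies (1193 expected, Table 3). The section then says: "We will perform the primary analyses in patients undergoing pancreatoduodenectomy and subsequently in all patients undergoing any type of pancreatic resection". It adds that "the total number of patients registered in this trial is expected to be 25% more than the required sample size".
- **Abstract, Methods.** The composite primary outcome "will be measured in a sample size of at least 1600 patients undergoing pancreatic resection".
- **Statistical analysis.** The contrast is described as "outcomes of all patients undergoing pancreatic resection before implementation of the algorithm (i.e. current practice) will be compared to outcomes of all patients" after implementation. The section uses a two-sided 0.05 in every analysis and removes wash-in patients from the primary analysis. Its adjusted covariates include whether the index operation was a pancreatoduodenectomy.
- **Subgroup and sensitivity analyses.** "Analyses will be performed both on the group of patients undergoing pancreatoduodenectomy and on the entire group" of resections; no ranking is given.
- **Interim analysis.** Halfway through the planned inclusion time the total number of inclusions is checked. "If the sample size is less than 47.5% of the target at that time", later steps are lengthened to keep 80% power.
- **Trial status.** On 8 November 2018: "569 patients included. Conclusion: enrollment as planned, trial continues without adaptation".

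**The concern.** A reader who starts from the abstract or the statistical analysis section would take all resections as the primary population. A reader who starts from the sample size section would take pancreatoduodenectomy. Both analyses are planned, both use 0.05, and nothing says what happens to the all-resection result if the pancreatoduodenectomy result is not significant. That leaves room to choose after the event which of two overlapping results is called primary.

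The same ambiguity reaches two numbers. The total in the abstract does not follow from the sample size section. The interim rule compares a count with a target without naming the resection type for either, and without saying whether wash-in patients are counted.

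**Working it through.** **1. Reproduce 1186.** Inputs from the sample size section: 13.8% falling to 6.9%, ICC 0.009, cluster autocorrelation 1, I = 17 clusters, T = 18 periods. The Hussey-Hughes variance of the effect is

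I·s·(s + T·t) / [(I·U − W)·s + (U² + I·T·U − T·W − I·V)·t],

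where s is the residual variance of a cluster-period mean and t the between-cluster variance. For this design U = 153 and W = V = 1785, so I·U − W = 816 and the second bracket is 7752.

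- Mean incidence 0.1035, so total variance = 0.1035 × 0.8965 = 0.09279.
- t = 0.009 × 0.09279 = 0.000835.
- Patients per cell = 1186/306 = 3.876, so s = 0.991 × 0.09279/3.876 = 0.02372.
- Variance = 0.000605, standard error = 0.0246, and 0.069/0.0246 − 1.96 = 0.845, giving power 0.80.

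Solving for exactly 0.80 gives 1183. The stated 1186 is sound for pancreatoduodenectomy.

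**2. Total.**
- 1186 × 1.25 = 1483; 1193 × 1.25 = 1491.
- 1600/1186 = 1.35, which is 35% more, not 25%. The gap is 1600 − 1483 = 117 patients.
- If the other resections were meant to be 25% of the total, 1186/0.75 = 1581 and 1193/0.75 = 1591. These are near 1600 but still below it, and the text does not say this.
- The audit's 1686 resections in two years (104.36 weeks) give 1686 × 92/104.36 = 1486 in 92 weeks, close to 1483.

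**3. Type I error for two overlapping tests at 0.05.** Take the two statistics as bivariate normal with correlation √(pancreatoduodenectomy share). This assumes equal information per patient. The error is 1 − P(|Z1| < 1.96 and |Z2| < 1.96).
- Share 1186/1483 = 0.80, correlation 0.894: 0.071.
- Share 1186/1600 = 0.741, correlation 0.861: 0.074.
- Fixed sequence, pancreatoduodenectomy first: 0.05.

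**4. Power in all resections.** Table 2 gives 12% for all resections. With a fall to 6% and the same ICC (assumption), the formula in step 1 gives 0.815 at 1482 patients and 0.839 at 1600.

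**5. Interim count.** Threshold: 0.475 × 1186 = 563.35.
- 569 as pancreatoduodenectomies: 569/1186 = 48.0%, above the threshold (47.7% of 1193).
- 569 as all resections: 569/1.25 = 455 or 569 × 0.75 = 427 pancreatoduodenectomies, which is 38.4% or 36.0% of 1186. Like for like, 569 is 38.4% of 1483 (704 needed) and 35.6% of 1600 (760 needed). All fall below 47.5%.
- Wash-in: the margin is 569 − 563.35 = 5.65. If six of the 569 were wash-in patients, 563/1186 = 47.47% would be just under the rule.

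**The case against.** The strongest reply is that the article does name its primary population. The sample size section gives a reason for choosing pancreatoduodenectomy, sizes the trial on it and analyzes it first. The sentence in the statistical analysis section can be read as defining the before-and-after contrast; the sentence there on the primary analysis concerns intention-to-treat and names no population. The subgroup section is compatible with that order. This stands as the most natural reading. It does not remove the abstract's statement about the primary outcome, and an order of analysis is not a rule about what may be claimed. A formal gate might sit in an analysis plan that is not shown, but sections that describe the population differently still need to agree.

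Four stronger readings are tempting and are not supported:

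- **That the type I error is 7%.** No section says either result may be claimed. The figure applies only if that were done, and its upper end uses the 1600 total that is itself in doubt.
- **That power is adequate only for pancreatoduodenectomy.** Step 4 shows otherwise.
- **That the resection-type covariate proves all resections are primary.** The adjusted model is described alongside the secondary endpoints, the covariate list comes from an all-resection model (Table 4), and a constant covariate simply drops out of a pancreatoduodenectomy fit.
- **That the interim decision was wrong and the trial is short of patients.** The rule is tied to 80% power, and the only number derived for 80% power is 1186. The look fell at 304 of 670 days (45.4%). On that pace 569 × 670/304 = 1254 by the planned end. As pancreatoduodenectomies that exceeds 1186, and × 1.25 it gives 1568 resections. As all resections, 1254 would fall well short of 1483. The reported conclusion therefore fits 569 pancreatoduodenectomies better, and a few wash-in patients in the count would not by themselves show a real shortfall.

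**Conclusion.** The point holds as a fault of definition and error control, not of power. Pancreatoduodenectomy is the intended primary population on the best reading, but the abstract and the statistical analysis section do not say so, and the status of the all-resection test is left open. The cost is an error rate of about 7% rather than 5% if either result were treated as primary; this rests on the normal approximation and a pancreatoduodenectomy share of 74–80%.

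The two stated totals conflict by 117 patients (about 1483 against at least 1600). The documents do not settle which is intended, although the audit rate favors the lower figure.

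The interim target is most plausibly 1186, and the decision to continue stands if the 569 were pancreatoduodenectomies outside wash-in. The article does not state this. If they were all resections, the 47.5% rule would have been triggered.

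**What to change.** - Name pancreatoduodenectomy outside the wash-in period (n = 1186) as the single primary analysis set in the abstract, the sample size section and the statistical analysis section.
- State that all resections are tested second, only if the primary test is significant, or label that analysis secondary.
- Use the resection-type covariate only in the all-resection model.
- Correct the abstract total to about 1480 resections, or correct the 25% if 1600 is intended.
- Define the interim count as pancreatoduodenectomies outside wash-in against 1186, and confirm from the database what the 569 counted. Do this while recruitment continues, because step length can be changed only until then.

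The cost is wording and one recount, with no extra patients. The downside is that the all-resection result is no longer a free-standing primary claim.
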